**Methods:**

Eligible participants are aged 16-17.33 years of age, have a learner’s permit in Pennsylvania, have practiced no more than 10 h, and have at least one parent/caregiver supervising. Participants are recruited from the general community and through the Children’s Hospital of Philadelphia’s Recruitment Enhancement Core. Teen-parent dyads are randomized 1:1 to Drivingly or usual practice control group. Drivingly participants receive access to an online curriculum which has 16 lessons for parents and 13 for teens and an online logbook; website usage is tracked. Parents receive two, brief, psychoeducational sessions with a trained health coach and teens receive an on-road driving intervention and feedback session after 4.5 months in the study and access to DriverZed, the AAA Foundation’s online hazard training program. Teens complete surveys at baseline, 3 months post-baseline, at licensure, 3months post-licensure, 6 months post-licensure, and 12 months post-licensure. Parents complete surveys at baseline, 3 months post-baseline, and at teen licensure. The primary end-point is police-reported MVCs within the first 12 months of licensure; crash data are provided by the Pennsylvania Department of Transportation.

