#### Surveys

Survey collection from teens will occur at baseline, 3 months post-baseline, licensure, 3 months post-licensure, 6 months post-licensure, and 12months post-licensure. Survey collection from parents will occur at baseline, 3 months post baseline, and at teen licensure. Survey collection will be done remotely, through REDCap. Missed survey responses may be followed up by phone, text, or email with the study team. Additionally, dyads will be asked to record/log their practice driving for 5–6 months post-baseline and prior to obtaining their driver’s license via a web-based e-learning platform (via the Drivingly WordPress platform). See Supplementary Table 1 for a summary of survey measures mapped to the Drivingly Conceptual Model. In addition, we measured driving exposure two ways at baseline, 3, 6, 9, 12 and 18 months with The Situational Driving Frequency Scale [37] to assess driving frequency in 14 situations using 5-point scale ranging from Never (0) to Very Often (4 to 7 days per week); total score 0–56 (teen report; parent report at Baseline only) and hours of driving per week was assessed using a write-in of hours driven Monday-Friday; Saturday and Sunday at (teen and parent report). Sociodemographic data were collected at baseline and included teen and parent gender, age, race and ethnicity, and parent’s relationship to teen, educational attainment, and current relationship status. Additional individual difference variables were collected but are not the focus of the main trial (e.g., sensation seeking) and are thus not reported here.

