If there is substantial item-level missingness in the survey data (e.g., in excess of 5%), we will assess whether non-response bias may be present; however, if we find such differences, we will use multiple imputation with chained equations as suggested by prior research under the relatively mild assumption of missingness at random [43].

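### Imputing survey data only after a non-response difference is found is a data-driven pretest that can leave the Hypothesis 2 and 3 analyses unimputed

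*Protocol article*

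**What the plan says.** The missing-data rule closes the Statistical plan section of the protocol article and concerns survey data only. It has two conditions in sequence.

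- The first is an amount of missingness, with the percentage offered as an example: "If there is substantial item-level missingness in the survey data (e.g., in excess of 5" per cent. Meeting it leads to a check, not to imputation: "we will assess whether non-response bias may be present".
- The second is the result of that check: "however, if we find such differences, we will use multiple imputation with chained equations as suggested by prior research". Imputation is then done "under the relatively mild assumption of missingness at random".

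The article does not say how a difference is to be judged, or which analysis is used when either condition fails.

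The Surveys section sets out the data concerned. Teens are surveyed six times: "Survey collection from teens will occur at baseline, 3 months post-baseline, licensure, 3 months post-licensure, 6 months post-licensure, and 12months post-licensure". Parents are surveyed three times. One exposure measure has many items, used "to assess driving frequency in 14 situations using 5-point scale". The Methods section names five process variables under Hypothesis 3. The Statistical plan analyses them as mediators with marginal structural models. The primary endpoint has another source: "crash data are provided by the Pennsylvania Department of Transportation".

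**The concern.** The rule uses a preliminary look at the trial data to choose between two analyses, and each condition looks at the wrong thing.

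The second condition treats a negative check as permission not to impute. A comparison of respondents with non-respondents can miss a real difference because few people are missing. It can examine only characteristics that were recorded. Even if there is truly no difference, imputation can recover precision, so a negative check is no reason to withhold it.

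The first condition is expressed at item level, whereas the usable sample depends on joint missingness across all variables in a model. Many small item-level losses can add up to a large loss of dyads without any item being conspicuous.

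At stake are the process effects in Hypothesis 2 and the indirect effects and proportions mediated in Hypothesis 3. These are the trial's test of its conceptual model, and they rest largely on surveys.

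**Working it through.** The plan gives no figure for this rule, so there is none to reproduce. The documents also give no survey missingness rates. What follows is illustration under stated assumptions.

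**Inputs.** From the Statistical plan: 1,200 dyads (600 per arm), the 5% example, and α = 0.05. From the Surveys section: a 14-item scale. Assumed: 4.9% missing on each variable, just under the example figure, and models using k = 5, 7 or 10 such variables.

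**Step 1: joint loss across variables.** With missing rate m on each of k variables, the fraction of dyads with all k observed is:

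- fully overlapping (the same dyads miss everything): 1 − m
- independent: (1 − m)^k
- fully disjoint (no dyad misses two): 1 − k·m

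With m = 0.049:

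| k | Overlapping | Independent | Disjoint |
|---|---|---|---|
| 5 | 95.1% | 0.951^5 = 77.8% | 1 − 0.245 = 75.5% |
| 7 | 95.1% | 0.951^7 = 70.3% | 1 − 0.343 = 65.7% |
| 10 | 95.1% | 0.951^10 = 60.5% | 1 − 0.490 = 51.0% |

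Of 1,200 dyads, overlap leaves about 1,141. Independence leaves about 933 (k = 5) to 726 (k = 10). Disjoint missingness leaves 906 to 612.

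**Step 2: effect on precision.** If standard errors scale with 1/√(fraction kept), they grow by these factors relative to full data:

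- overlapping: 1/√0.951 = 1.03
- independent: 1/√0.778 = 1.13 to 1/√0.605 = 1.29
- disjoint: 1/√0.755 = 1.15 to 1/√0.510 = 1.40

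These are ceilings on what imputation could recover; it would recover only part.

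**Step 3: the same point within one scale.** With 5% missing on each of the 14 items, the fraction with every item answered is 0.95^14 = 48.8% under independence, 95% under full overlap, and 1 − 14 × 0.05 = 30% if disjoint.

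**Step 4: how much a negative check can show.** At 5% missing, 60 of 1,200 dyads are non-respondents and 1,140 are respondents. The standard error of a standardised mean difference between them is √(1/60 + 1/1,140) = 0.132. If the check were a two-sided test at 0.05 (an assumption, since no criterion is given), an observed difference below 1.96 × 0.132 = 0.26 standard deviations would not count as found. A true difference of that size would be missed about half the time. For a single item this matters little: leaving out 5% who differ by 0.26 shifts the mean by only 0.05 × 0.26 = 0.013 standard deviations. So a negative check is weak evidence, and the larger practical exposure is the joint loss in step 1.

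**The case against.** The case on the other side is substantial, and much of it stands.

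- **No default is stated.** A reader might infer that complete-case analysis is the fallback. That is a natural inference, but the article never names it, and the full plan may specify something else.
- **The 5% is an example.** A reader might treat 4.9% as safely below a cut-off. The text says only that missingness should be substantial, so analysts facing a joint loss of 22% to 39% could call it so. This softens the first condition but leaves it undefined, and it does nothing for the second.
- **Missed survey waves.** A reader might conclude that whole missed surveys are left unhandled. The rule speaks of items, and the Surveys section offers only contact attempts: "Missed survey responses may be followed up by phone, text, or email with the study team". But a condensed article may leave this to the analysis plan, so it is not a finding. Nor do the documents support calling missed surveys the larger loss: the 10% dropout is an input to the crash power calculation, not a survey non-response rate.
- **The independence figures are not a prediction.** Non-response often clusters in the same people, which moves retention towards 95%. The article gives no variable count per model, and its mediation wording fits one mediator at a time.
- **Differential loss by arm is not documented.** Survey payments are equal in the two arms.

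What survives is the rule itself. It is stated, not omitted, and it makes the method depend on what a check of the data happens to find.

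**Conclusion.** The point holds for the survey-based Hypothesis 2 and 3 analyses. The article makes imputation depend on a pretest whose negative result does not justify analysis without imputation, and on an item-level quantity that does not track joint loss. Followed as written, the rule could leave those analyses unimputed where imputation under the plan's own missing-at-random assumption would be less biased or more precise.

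The size is uncertain. At 4.9% per variable, retention runs from 95% down to 51%, depending on how missingness overlaps and on an assumed 5 to 10 variables. If non-response is strongly clustered, little is lost. Bias is possible but not shown, and an unimputed analysis can be valid under some missingness patterns.

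A reader might extend this to the trial's main result. The documents do not support that: the crash endpoint comes from Department of Transportation records, and the planned hazard ratios are unadjusted, so this rule does not touch them. The change is worth making because it is cheap, but it concerns secondary analyses.

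**What to change.** Remove the condition that differences must first be found. State in advance that multiple imputation by chained equations is the method for the survey-based process and mediation analyses, whatever the non-response check shows. Include arm, baseline variables, the other survey waves and the crash outcome in the imputation model. Report the unimputed analysis as a sensitivity analysis. The non-response comparison can stay as a description of who is missing, but should no longer select the method.

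The cost is a change of plan wording and modest extra programming. No data collection changes, and the primary crash analysis stays as it is. Imputation still rests on missing at random, which the plan already accepts.

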### Data Safety Monitoring Board

The MPIs and select study team members will meet with a Data and Safety Monitoring Board (DSMB) biannually to ensure appropriate study progress, conduct, and safety. The DSMB is comprised of a Chair and two board members. Meeting minutes will be taken and drafted into a letter signed by the Chair. After each biannual meeting, the study teem will update procedures per the DSMB’s recommendation.

### Ethical review

This protocol was reviewed and approved by the IRB the University of Pennsylvania. Enrolment began on August 18, 2021 and is ongoing at the time of submission.

## Discussion

Although recruitment was delayed by the COVID-19 pandemic, enrollment has been robust. A number of infection control measures were taken by the study team, including masking and covid-screening protocols per the University of Pennsylvania’s COVID-19 and local guidelines where the ODAs take place, sanitation of training vehicles between each ODA, and air filtration systems in all communal spaces, but these have not negatively affected operations. The target completion date for the study is June 2025 and recruitment is on-going at the time of submission of this article for publication.

Young drivers’ crash risk is highly heterogeneous, changes non-linearly and non-incrementally, and the variability of the transportation environment in conjunction with its interconnected (i.e., systems) features make individual-level crash risk hard to predict [31]. Thus, a flexible, multicomponent, and sustained set of cohesive interventions stands the best chance to meaningfully reduce crash risk for the largest number of young drivers. Results from the main trial, which commenced in the summer of 2021, will help inform clear strategies to reduce motor vehicle crashes.

## Data Availability

The datasets used and/or analysed during the current study will be available from the corresponding author on reasonable request and de-identified data will be made available via a persistent link included with each publication.

## Abbreviations

MVC: Motor Vehicle Crash(es)
PA: DOT Pennsylvania Department of Transportation
